#### Data collection

Instruments to measure demographic information, anthropometric characteristics, self-efficacy, well-being and physical activity will be included in the battery. Data on literature-based demographic covariates of multidimensional well-being [43] will be collected at Time 1 and will include participant gender, age, race, education-level, marital status, and annual income. Zip code data will be collected as a proxy for a host of built environment factors that may be related to an individual’s level of physical activity [10]. Anthropometric data will be collected at all three time points and will be assessed by asking each participant his or her height and weight. Demographic, zip code, and anthropometric variables are collectively referred to as covariates from this point forward.

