#### Model A in more detail

Model A will impose a regression model for each proposed outcome with measures taken at Time 2 and Time 3 as the dependent variables. Covariates, the outcome at Time 1, and group allocation (FFW =1, UC = 0) will serve as predictors of the outcome at Time 2 and Time 3 and these regression coefficients will be estimated freely. Intercepts for the outcome at Time 2 and Time 3 will be estimated freely. Covariance between the error terms for the outcome at Time 2 and Time 3 will be estimated freely. The focal parameters will be the direct effects from group allocation to the outcome at Time 2 (γ_Time2_) and Time 3 (γ_Time3_). A positive focal parameter value will convey that the FFW group has a higher adjusted mean for the outcome as compared to the UC group.

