#### Model B in more detail

Model B will impose a latent class (with two classes) regression model with CACE estimation for each proposed outcome with measures taken at Time 2 and Time 3 as the dependent variables. The first class (i.e., Class 1) will be conceptualized as never-takers. The second class (i.e., Class 2) will be conceptualized as compliers. A dichotomous indicator of latent class (where 0 = non-compliers in the FFW group, 1 = compliers in the FFW group, and a missing value for participants in the UC group) will be generated. Compliance classification, modeled as a categorical latent variable, will be regressed on covariates. Covariates, the outcome at Time 1 and group allocation will serve as predictors of the outcome at Time 2 and Time 3 and these regression coefficients will be freely estimated in Class 1 and Class 2. The two direct effects from group allocation to the outcome at Time 2 and Time 3 will be fixed to 0 in Class 1 (i.e., the exclusion restrictions: γ_ntTime2_ = γ_ntTime3_ = 0), and will be estimated freely in Class 2 (i.e., γ_cTime2_, γ_cTime3_). The intercepts for the outcome at Time 2 and Time 3 will be estimated freely in each class. Covariance between the error terms for the outcome at Time 2 and Time 3 will be estimated freely in each class. The focal parameters will be the direct effects from group allocation to the outcome at Time 2 and Time 3 in Class 2 (i.e., γ_cTime2_, γ_cTime3_).

A positive focal parameter value will convey that compliers in the FFW group had a higher adjusted mean for the outcome as compared to potential compliers in the UC group.

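### The covariate definition does not limit height and weight to baseline, and the compliance regression leaves out the Time 1 outcome

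*Protocol article*

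**What the plan says.** In the protocol article, Data collection ties the demographic variables to baseline: they "will be collected at Time 1 and will include participant gender, age, race, education-level, marital status, and annual income". Height and weight are treated differently: "Anthropometric data will be collected at all three time points". Table 1 (the SPIRIT flow diagram) agrees, marking both at days 0, 30 and 60. The section then closes with the definition used in all later modelling: "Demographic, zip code, and anthropometric variables are collectively referred to as covariates from this point forward".

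Model A in more detail reads: "Covariates, the outcome at Time 1, and group allocation (FFW =1, UC = 0) will serve as predictors of the outcome". Model B in more detail repeats this for both latent classes: "Covariates, the outcome at Time 1 and group allocation will serve as predictors of the outcome at Time 2 and Time 3". For class membership, Model B says: "Compliance classification, modeled as a categorical latent variable, will be regressed on covariates". Model C keeps every parameter of Model B and only relaxes the exclusion restriction, so it inherits both specifications.

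**The concern.** There are two separate matters.

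**Timing of the anthropometric covariates.** Weight at 30 or 60 days is measured after allocation, and FFW is meant to raise physical activity, so weight may respond to it. If later weight entered as a predictor, the coefficient for allocation in Model A would no longer be the intention-to-treat effect that the Data analytic approach promises; any part of the effect associated with weight change would be removed. In Models B and C the same covariates also predict compliance class. Class is unobserved in the usual care arm and is inferred partly from covariates. It is meant to be fixed before treatment, so a variable that engagement itself may alter is not a proper predictor of it.

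**Predictors of compliance class.** The Time 1 outcome predicts the later outcomes but is not listed for compliance. If baseline well-being or self-efficacy predicts who engages, information on class that has already been collected goes unused, and the complier effect is estimated less precisely. The Statistical power estimation section expects engagement below 50%, which is where the plan favours the complier models.

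**Working it through.** **1. The text.** Demographics carry a Time 1 limit. Height and weight carry all three time points. The next sentence pools them as covariates with no limit. The model sections attach Time 1 to the baseline outcome but nothing to the covariates. The literal reading therefore admits Time 2 and Time 3 weight, although no sentence says they will be entered.

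**2. The plan's own figure.** Table 2 gives power for the complier effect; for d = 0.20 at Time 2 it is 0.32, 0.54 and 0.74 at 25%, 45% and 65% engagement. From the stated inputs, 900 × 0.65 = 585 are observed, or 292.5 per arm. With a two-sided α of 0.05 (sidedness assumed) and no variance explained by covariates:

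- Effect diluted to d × engagement: 0.088, 0.192, 0.349.
- Class treated as known in both arms (n × engagement): 0.226, 0.368, 0.496.
- Known class with an assumed R² of 0.36: 0.327, 0.527, 0.684.

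None of these reproduces all three entries. The article does not give the population R² or the class separation, so Table 2 can be neither rebuilt nor faulted, and it does not bear on this point.

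**3. Size of the attenuation if Time 2 weight were a predictor.** Let d_w be the effect of allocation on weight change in SD units, ρ the correlation of weight change with the outcome given baseline and arm, and s the residual SD of the outcome. Then

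bias ≈ −d_w × ρ × s.

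The documents give none of these. Assumed: s = 0.8; d_w and ρ both negative (FFW lowers weight; lower weight goes with a better score). For d_w = −0.1 and ρ = −0.3, bias = −(0.1 × 0.3 × 0.8) = −0.024. A least-squares simulation of Model A with a true effect of 0.20 gave:

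| d_w | ρ | Formula bias | Estimate with Time 2 weight |
|---|---|---|---|
| 0 | 0 to −0.3 | 0 | 0.199–0.202 |
| −0.1 to −0.5 | 0 | 0 | 0.197–0.200 |
| −0.1 | −0.1 | −0.008 | 0.191 |
| −0.1 | −0.3 | −0.024 | 0.174 |
| −0.2 | −0.1 | −0.016 | 0.184 |
| −0.2 | −0.3 | −0.048 | 0.152 |
| −0.5 | −0.1 | −0.040 | 0.161 |
| −0.5 | −0.3 | −0.120 | 0.082 |

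For d_w of −0.1 to −0.2 with ρ of −0.1 to −0.3, the formula loss is 0.008/0.20 = 4% to 0.048/0.20 = 24%. The −0.5 rows only mark the end of the range. With baseline weight alone the estimate was 0.197 to 0.203 in every scenario.

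**4. Cost of omitting the Time 1 outcome from the compliance regression.** A simplified one-time-point Model B (exclusion restriction kept, true complier d = 0.20, 585 observed, 400 replicates per scenario) was fitted with and without the Time 1 outcome in the class regression. Variance ratios, included over omitted:

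- Unrelated to engagement: 0.99 to 1.04. This shows the simulation noise.
- Weak to moderate association: 0.89 to 0.99. For example, at 25% engagement the SD fell from 0.253 to 0.239, and (0.239/0.253)² = 0.89.
- Log-odds 0.5 per SD: 0.92 to 0.96. A further run at 25% engagement gave (0.211/0.226)² = 0.87.
- Log-odds 1 per SD: 0.75 to 0.84. A further run at 45% engagement gave (0.118/0.133)² = 0.79.

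Across the null and the weak-to-moderate scenarios, the mean estimate moved by at most 0.003 (0.180–0.221 omitted, 0.182–0.219 included; Monte Carlo SE 0.007–0.013). No bias was detectable. Model C was not simulated.

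**The case against.** The strongest reply is that the article nowhere says later weight will be entered. Data collection lists what is gathered and gives the group a name. Compliance class in the complier framework is a pre-treatment stratum, so regressing it on covariates makes sense only with baseline values, and the ordinary reading is Time 1 height and weight. That stands, which is why the point concerns a definition and not a demonstrated bias. It does not remove the ambiguity: the definition directly follows the sentence on three time points, and the authors did write Time 1 where they meant it for the outcome.

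The size is also conditional. Bias needs both an effect on weight within 30 to 60 days and a link from weight to the outcome. The documents support neither with a figure, and weight is not a listed outcome. Adult height is not expected to respond. Missing later weight adds little, because those who skip a battery lack that battery's outcome too.

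On the compliance regression, the Time 1 outcome is already in the outcome regression of both classes, and the plan says alternate specifications will be considered. The omission is therefore a matter of precision, not an error.

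A reader might also infer that zip code enters as a raw label or nominal factor and makes the models inestimable. The text does not support this. It says only: "Zip code data will be collected as a proxy for a host of built environment factors". That fits a derived area-level variable at least as well, and an article may leave coding to the full plan.

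**Conclusion.** The point holds as a loosely fixed definition with an easy remedy. The literal wording admits post-randomisation weight as a predictor in Models A to C, both for the outcomes and for compliance class. If followed, it would attenuate the effect of allocation by about 4–24% under the assumed weight-change effects of 0.1–0.2 SD, and not at all if FFW does not move weight or weight is unrelated to the outcome. It would be wrong to conclude that the trial plans to adjust for later weight or that its estimates will be biased.

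The absence of the Time 1 outcome from the compliance regression is stated plainly. Its cost is precision only: about 0–10% of the variance for a moderate association with engagement (one run gave 13%), roughly 15–25% for a strong one, and none if it is unrelated. These figures rest on assumed associations and a simplified Model B. Taken together, this is a low-cost improvement and does not call the design or the analysis approach into question.

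**What to change.** In Data collection, define the covariates as Time 1 demographics and Time 1 height and weight (or BMI), and state that Time 2 and Time 3 weight is never used as a predictor. How zip code is handled can stay as the full plan has it.

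In Model B in more detail, have compliance class *regressed on covariates and the outcome at Time 1*. Model C follows automatically.

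Both are changes of wording. They need no new data, and the Time 1 outcome is already collected. If baseline values were always intended, the first change alters nothing. If the Time 1 outcome proves unrelated to engagement, the second showed no material loss of precision (variance ratio 0.99 to 1.04).

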##### Self-efficacy to comply

Following completion of the four introductory challenges, each participant assigned to the FFW group will be asked to respond to the following item: *How confident are you in your current ability to get yourself to complete at least 15 Fun For Wellness post-introductory challenges within the next 30 days?* A five category rating scale structure, where 0 = no confidence, 1 = low confidence, 2 = moderate confidence, 3 = high confidence and 4 = complete confidence, will be implemented for this item, and in all self-efficacy scales from this point forward, based on previous research on effective self-efficacy rating scale structures [44]. Asking a participant at the onset of an intervention to estimate their potential engagement with the forthcoming intervention is consistent with some related previous research on compliance [45].

##### Well-being self-efficacy

Well-being self-efficacy will be measured at Time 1 through Time 3 with an expanded version (i.e., from 7-items to 21-items) of the WBSE scale as recommended in the literature [26]. The expanded version of the WBSE scale is highly concordant with subjective well-being as conceptualized in the FFW context (i.e., evaluated with the I COPPE scale). Specifically, the seven dimensions of well-being self-efficacy purported to be measured by the WBSE scale – interpersonal, community, occupational, physical, psychological, economic and overall – match the seven dimensions of subjective well-being purported to be measured by the I COPPE scale. Each of the seven dimensions of well-being self-efficacy purported to be measured by the WBSE scale has an exclusive item stem that references three unique periods of time: past (i.e., 30 days ago), present (i.e., right now), and future (i.e., 30 days from now). Reference to the past, present, and future is an established practice in the assessment of subjective well-being related constructs in general [46, 47] and in the FFW context [27, 48]. Estimates of the validity and reliability of scores resulting from answers to the original WBSE scale have been provided [26]. Estimates of the validity and reliability of scores resulting from answers to the expanded version of the WBSE scale, however, will not be available prior to data collection at Time 1. Evidence for the reliability and validity of responses to the expanded version of the WBSE scale will be evaluated prior to testing either the primary or secondary hypotheses.

##### Well-being actions self-efficacy

Well-being actions self-efficacy will be measured at Time 1 through Time 3 with the well-being actions self-efficacy (WBASE) scale, which is a newly developed 18-item instrument. The WBASE scale was designed to measure well-being actions self-efficacy as conceptualized in the FFW intervention. The WBASE scale is highly concordant with well-being actions as conceptualized in the FFW context (i.e., evaluated with the I COPPE actions scale). Specifically, the six dimensions of well-being actions self-efficacy purported to be measured by the WBASE scale – interpersonal, community, occupational, physical, psychological, and economic – match the six dimensions of well-being actions purported to be measured by the I COPPE actions scale. Each of the six dimensions of well-being actions self-efficacy purported to be measured by the WBASE scale has three items designed to measure it. Estimates of the validity and reliability of scores resulting from answers to the WBASE scale will not be available prior to data collection at Time 1. Evidence for the reliability and validity of responses to the WBASE scale, however, will be evaluated prior to testing either the primary or secondary hypotheses.

##### Physical activity self-efficacy

Physical activity self-efficacy will be measured at Time 1 through Time 3 with the physical activity self-efficacy (PASE) scale, which is a slightly modified version of the 8-item exercise self-efficacy (EXSE; [35]) scale. The EXSE scale assesses an individual’s beliefs in their ability to continue exercising on a three time per week basis at moderate intensities for 40+ minutes per session in the future. The PASE scale was tailored for the FFW context to assess the degree to which an individual perceives that they have the capability to engage in a recommended amount of weekly physical activity for health. The PASE scale is highly concordant with physical activity as conceptualized in the FFW conceptual model (i.e., measured by the IPAQ) in that it measures weekly physical activity across four general domains of life: leisure time (12-items), domestic and gardening (12-items), work-related (12-items), and transport-related (12-items). Each of the four domains has two unique stems (e.g., how confident are you in your current ability to engage in leisure related physical activity at a vigorous level of intensity) that reference six increasing time periods (e.g., for at least 10 or 15 or 30 or 45 or 60 or 75 min in the next week). Estimates of the validity and reliability of scores resulting from answers to the PASE scale will not be available prior to data collection at Time 1. Evidence for the reliability and validity of responses to the PASE scale, however, will be evaluated prior to testing either the primary or secondary hypotheses.

##### Self-efficacy to regulate physical activity

Self-efficacy to regulate physical activity will be measured at Time 1 through Time 3 with the self-efficacy to regulate physical activity (SERPA) scale, which is a slightly modified version of the 13-item barriers self-efficacy (BARSE; [36]) scale. The BARSE scale assesses an individual’s perceived capabilities to exercise three times per week for 40 min over the next 2 months in the face of commonly identified barriers to participation. The SERPA scale was tailored for the FFW context to assess the degree to which an individual perceives that they have the capability to overcome possible barriers to engagement in a recommended amount of weekly physical activity for health. The SERPA scale is highly concordant with physical activity as conceptualized in the FFW conceptual model (i.e., measured by the IPAQ). Estimates of the validity and reliability of scores resulting from answers to the SERPA scale will not be available prior to data collection at Time 1. Evidence for the reliability and validity of responses to the revised SERPA scale, however, will be evaluated prior to testing either the primary or secondary hypotheses.

##### Subjective well-being

Subjective well-being will be measured at Time 1 through Time 3 with the 21-item I COPPE scale, which is available in Prilleltensky et al. [27]. Each of the seven dimensions of subjective well-being purported to be assessed by the I COPPE scale – interpersonal, community, occupational, physical, psychological, economic and overall – is measured with an exclusive item stem that references three unique periods of time: past (i.e., 30 days ago), present (i.e., right now), and future (i.e., 30 days from now). Responses to each item are organized within an 11-point Likert scale that ranges from 0 (*worst your life can be*) to 10 (*best your life can be*). Estimates of the validity and reliability of scores resulting from answers to the I COPPE scale have been provided [1, 27, 33, 48]. The Optum™ SF-36v2 Health Survey [49] will also be included in the battery for possible exploratory purposes.

##### Well-being actions

Well-being actions will be measured at Time 1 through Time 3 with an expanded version (i.e., from 12-items to 18-items) of the I COPPE actions scale [32]. The I COPPE actions scale was expanded from 12-items to 18-items to match the WBASE scale. Each of the six dimensions of well-being actions purported to be measured by the I COPPE actions scale – interpersonal, community, occupational, physical, psychological, and economic – has three items designed to measure it. Responses to each item are organized within a 7-point Likert scale that ranges from 0 (*never*) to 6 (*always*). Estimates of the validity and reliability of scores resulting from answers to the original 12-item I COPPE actions scale have been provided [31, 32]. Estimates of the validity and reliability of scores resulting from answers to the expanded version of the I COPPE actions scale, however, will not be available prior to data collection at Time 1. Evidence for the reliability and validity of responses to the expanded version of the I COPPE actions scale will be evaluated prior to testing either the primary or secondary hypotheses.

##### Physical activity

Physical activity will be measured at Time 1 through Time 3 with the long form (i.e., 27-items) of the IPAQ [39, 40]. The long form of the IPAQ is intended for individuals from 15 to 69 years old and purports to measure physical activity in four domains – leisure time, domestic and gardening, work-related, and transport-related – according to the frequency and duration of the physical activity performed in each domain during a week. The physical activities measured are separated according to their intensity, which is defined as a distinction between walking, moderate physical activities, and vigorous physical activities. Moderate activities are those that cause a small increase in respiratory frequency and require moderate physical exertion, and vigorous activities cause more breathing than normal, with hard physical exertion [40]. Physical activity scores will be created based on IPAQ data processing guidelines [50].

### Data analytic approach

Evidence for the reliability and validity of responses to each revised (e.g., WBSE scale) or new (e.g., WBASE scale) instrument will be evaluated prior to testing either the primary or secondary hypotheses consistent with standards for psychological testing [51]. Exploratory structural equation modelling will be used to fit Time 1 data [52]. Latent variable reliability will be measured with coefficient *H* [53]. Composite score reliability will be assessed with coefficient omega [54] and coefficient alpha [55].

To test the a priori hypotheses previously stated, three general models will be fit for each primary and secondary outcome in M*plus* 8.0 [56]. The estimator for each model will be maximum-likelihood with standard errors that are robust to conditional non-normality. In each model the main focus will be to examine the mean difference between the FFW group and the UC group on a proposed outcome at both Time 2 and at Time 3. Alternate specifications to each model will also be considered to examine some model-based assumptions [57]. The first model (i.e., Model A) will follow an intent-to-treat approach [58] by estimating the effect of being allocated to the treatment (i.e., FFW in this case) condition (i.e., ITT or γ). The second model (i.e., Model B) will follow a complier average causal effect (i.e., CACE) approach [59–62] by estimating the effect of being allocated to the treatment (i.e., FFW in this case) condition for compliers with the FFW intervention (i.e., γ_c_). The third model (i.e., Model C) will follow a CACE approach by estimating the effect of being allocated to the treatment (i.e., FFW in this case) condition for non-compliers with the FFW intervention (i.e., γ_nt_) in addition to estimating γ_c._ Fitting Model C provides a way of evaluating the sensitivity of Model B [45]. Model B and Model C both employ CACE estimation, where non-compliers will be conceptualized as never-takers consistent with CACE methodology based assumptions detailed in relevant literature [59–62]. If level of engagement is below 50% then a CACE approach (e.g., Model B and C) will be favored [63]. If level of engagement is at least 50% then an ITT approach (e.g., Model A) will be favored [63]. For exploratory hypotheses bias-corrected bootstrapped estimates of 95% confidence intervals for indirect effects within a path model will be obtained with the number of draws set equal to 2000 under an ITT approach [64]. Missing data (e.g., dropout) will be reported (e.g., in a flow diagram) and modeled consistent with the missing at random assumption [65] consistent with previous FFW research [1].

